## Abstract

**Background:**

Within high income countries, mental health is now the leading cause of long term sickness absence in the workplace. Managers are in a position to make changes and decisions that have a positive effect on the wellbeing of staff, the recovery of employees with mental ill health, and potentially prevent future mental health problems. However, managers report addressing workplace mental health issues as challenging. The aim of the *HeadCoach* trial is to evaluate the effectiveness of a newly developed online training intervention to determine whether it is able to build managers’ confidence to better support individuals within their teams who are experiencing mental ill health, and the confidence to promote manager behaviour likely to result in a more mentally healthy workplace.

**Methods/Design:**

We will conduct a cluster randomised control trial (RCT) to evaluate the effect of *HeadCoach*, an online training intervention for managers with a focus on the mental health of their employees, compared to a waitlist control. The target sample is 168 managers, and their direct employees. Managers and employees will be assessed at baseline and at 4-month follow up. Managers will have an additional, intermediate assessment 6-weeks post-baseline. The primary outcome is change from baseline in managers’ self-reported confidence when dealing with mental health issues within their team and promoting a mentally healthy workplace. The difference between the intervention and waitlist control groups will be assessed using linear mixed effects repeated measures (MMRM) analysis of variance (ANOVA). Secondary managerial outcomes include mental health literacy, attitudes towards mental health issues in the workplace and managerial behaviour in dealing with mental health matters with their staff. Employee outcomes will be perceived level of manager support, engagement, psychological distress, and rates of sickness absence and presenteeism.

**Discussion:**

To our knowledge this will be the first RCT of a purely online training intervention developed specifically for managers that promotes confidence to both support staff experiencing mental ill health and create a mentally healthy work environment. If successful, this intervention has the potential to provide an effective and efficient method of training managers in workplace mental health and to enhance employee wellbeing.

**Trial Registration:**

Australian and New Zealand Clinical Trials Registry ACTRN12617000279325

## Background

Mental ill health has become the leading cause of long-term sickness absence and work incapacity in many high income countries [1–3]. The most common mental conditions in the workplace are treatable and often preventable conditions including depression, anxiety, and stress-related disorders [4–6]. For some workers, the development or persistence of their mental health condition may, in part, be related to their workplace [7]. Conflicting and excessive work demands, a lack of job control, and poor collegial relationships and support have all been identified as primary sources of work-related stress that can impact upon employees’ well-being and productivity [8]. Many of these risk factors have the potential to be influenced by managers or other supervisors in the workplace. Positive leadership behaviour has also been identified as reducing the risk of sickness absence and as one of the determinants of employees returning to work following a period of sickness absence [1, 9].

Managers are in a unique position to manage work-based mental health risk factors and improve the mental health of their workers. Their knowledge of workplace issues, their ability to implement adjustments to working conditions, and their position to lead by example with regards to acceptance and understanding of mental health issues can influence changes and decisions to benefit their workers. As a result, managers may be able to implement reactive and preventative managerial strategies through primary, secondary and tertiary interventions as a means to enhance their employees’ mental health and to aid the recovery process of those workers who have become unwell [10, 11].

Best practice guidelines are available outlining the role managers should play in sickness absence, regardless of the underlying cause of the illness [12, 13]. These include, but are not limited to, behaviours that facilitate regular conversations with an employee, maintaining a focus on the employee’s well-being and being able to develop an appropriate return to work plan. However, managers often report feeling unsure what to do when a staff member is ill, particularly if they are suffering from a mental illness [5, 13]. Guidance is also available detailing how managers can modify their behaviour and the overall psychosocial work environment in order to reduce mental health risk factors for their staff [13, 14]. In line with this, agencies such as the Health and Safety Executive in the UK have provided management standards and descriptions of good practice across six areas of work that can impact negatively on employee health if not managed properly [14]. These areas of work design concern demands of the job, having a sense of control of duties, availability of workplace support, role clarity, communication within the organisation, and the promotion of positive working relationships. By effectively managing these primary sources of stress at work, managers can promote high level of health, well-being and organisational performance. However, once again, it is not clear how many managers utilise this advice and many report feeling unsure of how to best implement these ideas [5, 13].

A small body of research, comprising a number of pilot studies and a few small scale controlled trials, has evaluated specialised training programs for managers to promote understanding of mental health problems among workers, with evidence suggesting that managers value and benefit from such initiatives [2, 3, 15–17]. However, other controlled trials have not found any positive effects in terms of changing the attitudes of managers [11] and have failed to find any evidence that mental health training for managers has an impact on either their managerial behaviour of mental health matters or on objective measures of mental health amongst their direct reports [18, 19].

There is increasing recognition that best practice in workplace mental health requires an integrated approach that prevents harm, promotes positive mental health, and addresses mental health in the workplace regardless of the cause of the illness [8]. However, to date, the way in which these key components can be delivered together through manager training has not been well-articulated, resulting in either a lack of manager education or separate uncoordinated educational programs.

The current trial will test an integrated and comprehensive online training intervention for managers called *HeadCoach.* The use of online technology through a mobile and desktop compatible website will provide a number of benefits compared with traditional modes of workplace training [20]. Although there is limited personal interaction with educators and other participants, which can be a key component to effective learning, web-based training offers a greater deal of flexibility which is suitable for organisational based learning. It reduces the time commitment and impact on organisational resources by removing factors such as time taken to travel to and from training and the impact of having a large number of managers away from their jobs simultaneously. Online training allows participants to schedule training around the demands of their job, and course material can be revisited as required providing a greater opportunity for consolidation of content.

*HeadCoach* will be delivered to managers with a focus on how to best support the mental health needs of employees reporting directly to them. The primary aim of this trial is to evaluate the effectiveness of the *HeadCoach* intervention to improve managers’ confidence to effectively respond to the needs of staff experiencing mental health issues and to implement evidence-based managerial techniques that promote a more mentally healthy workplace.

## Methods/Design

### Study design

*HeadCoach* will be evaluated via a cluster randomised controlled trial (RCT) conducted within three industry partner organisations. Clusters will comprise of groups of managers based on organisational-specific pre-existing geographical work zones to reduce the risk of contamination between the intervention and control groups. Stratification will occur based on the number of managers within each zone for each industry. A researcher independent from the trial will use a computer-generated program to conduct the stratified randomisation of workplace zones prior to recruitment. Outcome data will be collected from the managers and from employees who report directly to them.

### Intervention

The *HeadCoach* online training intervention aims to build managers’ confidence in dealing with mental health issues in the workplace. This includes managers’ confidence when responding to mental illness and/or distress amongst their staff, and the implementation of behaviours supporting more mentally healthy workplaces to help prevent new mental health problems. Building confidence across these reactive and preventative managerial strategies to better manage mental health issues in the workplace is a key step in altering managers’ behaviours across these domains [21]. Improving confidence is also one of the central concepts of Self-Efficacy Theory, which suggests that people are more likely to engage in particular behaviours across a range of settings when they feel more capable of successfully attaining the intended outcome [22].

The intervention is self-guided and divided into three broad topics to be completed sequentially. The first topic, *Common mental illnesses*, provides an introduction to mental health issues commonly found in the workplace. The next topic, *How to help an employee you are concerned about*, discusses ways managers can identify people within their team who may be at risk of mental health issues, how managers can support their workers, and direction around how to best have a conversation with employees who may be experiencing mental ill health. It also discusses how to help employees stay at work or return to work faster following a period of sickness absence due to mental illness. The third and final topic, *Minimising mental health risks in the workplace,* examines managerial skills that are useful in reducing mental health risk factors in the workplace in order to create a mentally healthy workplace for all employees.

Each topic comprises between three and seven 10-min modules featuring text, activities, short videos, and practical exercises for individuals to complete. The course outline listing the twelve modules, three topic consolidation exercises and three topic toolboxes providing quick access to useful resources presented in that topic, is outlined in Table 1. Depending on individual learning styles, the entire program is expected to take approximately 2.5 hours to complete. It has been designed so managers can work through the content at their own pace across a 6-week period. The intervention will be delivered online through a mobile responsive website and can be accessed using a desktop, laptop, tablet, or smart phone.

**Table 1 Tab1:** Course outline for *HeadCoach*

*HeadCoach* Manager Training	
Topic 1: Common Mental Illnesses	
Module 1: Recognising Mental Health Issues	
Module 2: The Workplace and its People	
Module 3: Topic Summary Exercises	
Module 4: Topic Toolbox	
Topic 2: How to Help an Employee you are Concerned About	
Module 1: Identifying People at Risk	
Module 2: Providing Support	
Module 3: Having the Talk	
Module 4: Facilitating Help Seeking	
Module 5: Modifying Work to Help Recovery	
Module 6: Returning to Work	
Module 7: Topic Summary Exercises	
Module 8: Topic Toolbox	
Topic 3: Minimising Mental Health Risks in the Workplace	
Module 1: How to be a Respectful and Responsible Manager	
Module 2: Managing and Communicating Existing and Future Work	
Module 3: Managing Individuals within your Team	
Module 4: Managing Difficult Emotions	
Module 5: Topic Summary Exercises	
Module 6: Topic Toolbox	

### Participants

We aim to recruit both managers and their direct reports from three large industry partner organisations collaborating with this trial. These industry partners come from the emergency services and construction sectors. Together they have 690 managers and 9100 employees reporting directly to these managers who could potentially participate in the trial.

### Inclusion criteria

To be included in the study, participants must be 18 years or older; currently residing in Australia; have good English comprehension; and be a current employee of one of the three collaborating industry partners. In addition, participants in the manager group must supervise a team of three or more employees.

### Recruitment process

The process of recruitment will commence with each industry partner distributing an introductory email about the trial to managers at a certain level within each organisation and their direct employees describing the purpose of the research, outlining what is involved in the trial participation, and emphasising the voluntary nature of participation. It will discuss the proposed benefits of the trial to the individual and the industry, outline the independence of the research team from their employer, and advise that all components of the trial may be completed during work hours. Confidentiality of participation and data from their employer is assured.

Within the following week, all direct report employees of the managers within each cluster will receive an email from the research team inviting them to participate in the research study. This email will contain a link to the online research platform which employees can click to opt into the study and commence participation. At the completion of the recruitment period for direct report employees, participants at the managerial level will receive a manager-specific email invitation. This staggering of recruitment is designed to ensure that baseline employee data is obtained prior to the managers receiving any intervention. This email will invite managers to take part in the evaluation of an online educational training program about mental health in the workplace. As with the employee recruitment email, this email will include a link for managers to click if they choose to opt into the study.

### Trial procedure and assessment

Figure 1 outlines the trial procedure and stages of assessment for participants at the manager and employee levels.

**Fig. 1 Fig1:**
[figure not shown]
Participant flow-chart for the *HeadCoach* trial

#### Employees

Direct report employees who opt into the trial and provide consent via an online consent form will complete a 10-min baseline questionnaire. Demographic details, as well as information relating to own mental health, perceived level of manager support, self-reported absenteeism and presenteeism, psychosocial safety climate and work engagement will be collected. The completion of this baseline questionnaire will be the only requirement for employee level participants until the 4-month follow-up questionnaire. This follow-up questionnaire will be distributed by email and will contain the same assessment items as the baseline questionnaire. A unique code assigned to employee email addresses will be used to maintain participants’ privacy while allowing pre-post data to be linked. Employees who complete the 4-month employee questionnaire will indicate at the completion of the questionnaire whether they wish to be entered into a prize draw for one of three $250 vouchers by providing their name and contact details, with reassurances that this information will be kept separately from their responses and not disclosed to their employer.

#### Managers

At the completion of the baseline data collection period for employees, managers will be invited by email to participate in the study irrespective of whether their employees responded to the baseline questionnaire. Managers who agree to participate and provide online consent will create their individual *HeadCoach* registration account and complete a baseline assessment questionnaire. Demographic details and self-reported information on mental health literacy, attitudes towards mental health issues, confidence in dealing with mental health issues within the workplace, managerial practices used to support the mental health needs the team, and demographic details will be collected. Managers in the intervention group will then be directed into the online *HeadCoach* manager training program while those managers in the control group will be advised they will receive access to the training after a waiting period.

Post intervention questionnaires will be disseminated by email to the intervention and control groups at 6-weeks after completion of the baseline questionnaire. This 6-week period comprises the training period allocated to managers to complete *HeadCoach*. If a manager finishes all components of the online program earlier in the 6-week training period, they will be invited to complete the questionnaire at that earlier point of completion. This approach is expected to prevent non-response and ensure an accurate measure of the post intervention effect.

At the 4-month post-baseline assessment, a final data collection for the primary outcomes and other measures will be conducted for all managers and employees participating in the trial. An email will be sent to all manager and employee level participants inviting them to complete the final questionnaire, and to advise of a prize draw offered for its completion. Managers who complete the 4-month post questionnaire will be entered into a separate prize draw from the employees, for one of three $250 vouchers. Following the completion of all data collection, managers in the waitlist control group will be provided with online access to the *HeadCoach* program.

### Outcome measures

Managers and employees will complete separate questionnaires at each time point. Data will be collected via a secure, encrypted online research platform and de-identified to maintain the privacy of participants.

#### Primary outcome

The primary outcome is managers’ self-reported confidence when responding to staff members experiencing mental health problems and when considering how to alter the workplace environment in order to enhance employee mental health and well-being. Managers’ level of confidence will be assessed at 6-week and 4-month follow-ups, with the primary outcome being considered at 4-months post baseline. Confidence in managing mental health issues and promoting a mentally healthy workplace will be measured using a modified version of a previously published supervisor scale [10]. This scale describes six workplace scenarios and asks managers to indicate their level of confidence in dealing with each of these, on a five-point Likert scale ranging from *not at all* to *extremely confident.* This results in an overall confidence score ranging from 6 to 30. The types of scenarios asked about include “Initiating contact with staff on sickness absence leave that you believe might be due to mental illness” and “Creating a work environment that prevents and reduces stress within my team”*.* The wording of these vignettes aims to focus on managers’ self-efficacy and perceived confidence. As noted above, self-efficacy and confidence are thought to be key determinants of behaviour modification [22], with evidence suggesting that building confidence in managing workplace mental health problems can increase managers’ promotion of positive mental health within their teams [21].

#### Secondary outcomes

At each of the data collection points, information on a range of secondary outcomes will be assessed at the manager level. Measures that will be used to help understand the reasons for any shift in confidence include: knowledge about common mental health problems (measured using the Mental Health Knowledge Schedule (MAKS)) [23]; stigmatising attitudes towards mental illness (using a modified version of previously published personal stigma scales) [24–26]; and understanding of their role as a manager in dealing with mental health in the workplace [12]. Additionally, a range of secondary outcomes will be used to measure any changes in managers’ behaviour. Our ability to reliably measure managers’ behaviour in the workplace is limited by a number of key factors. By definition, a managers’ responsiveness to and support for staff experiencing mental health issues can only be measured once an employee develops and discloses mental health symptoms. It is likely that within a four-month trial, this would only occur for a minority of managers. This is the main reason that confidence regarding future behaviour is the primary outcome in this study. However, when a manager has experienced a staff member with mental health problems they will be asked how they responded. In addition, all managers will complete a questionnaire that seeks to enquire about their responsiveness to mental health problems in the workplace (for example “I initiate a conversation with individuals I supervise about their mental health and well-being”*)* with options on a five-point Likert scale ranging from *strongly disagree* to *strongly agree*. Managers will also be asked how often they apply a range of managerial techniques that promote a mentally healthy workplace using an adapted version of the HSE Management Standards Indicator Tool [14]. Finally, managers’ own level of psychological distress will be assessed with the Kessler Psychological Distress Scale (K6) [27].

Secondary outcomes will also be assessed at the employee level, although we acknowledge the possibility that any beneficial impact on employees may not be seen within the timeline of this type of study. Employees’ self-reported levels of well-being and psychological distress will be assessed by the 7-item Short Warwick-Edinburgh Mental Well-Being Scale [28] and the 6-item Kessler Psychological Distress Scale (K6) [27] respectively. Rates of absenteeism will be measured using employees’ self-report of recent sickness absence, and items from the World Health Organisation HPQ (WHOHPQ) Presenteeism Questionnaire [29] will be used to measure employees’ work performance. Employees’ perceived level of support from managerial staff will be measured through the Psychosocial Safety Climate Scale [30] and the manager scales on a workplace social support scale [31, 32]. Level of employee work engagement will be measured through a variation of the Utrecht Work Engagement Scale used in previously conducted work engagement surveys [33].

Demographic information including age, gender, job role and length of service in this role will also be collected for managers and employees.

### Statistical analysis

Primary analyses will be undertaken within an intent-to-treat framework, retaining all participants as randomised, regardless of extent of engagement with training or withdrawal from the study. Likelihood based methods (mixed-model repeated measures (MMRM)) will be used to assess significance of change in the two primary manager outcome measures. Clustering will be accommodated by a random cluster membership (work site) factor. A priori planned comparisons of change from baseline to the 4-month endpoint will test the primary hypothesis. An unstructured variance-covariance matrix will be used to accommodate relationships between observations at different occasions of measurement. Stratification variables and any variables found to be substantially imbalanced between intervention arms post randomisation will be tentatively included in these models and retained if statistically significant and influential on outcomes. Length of time from baseline to complete training and associated post-intervention assessment will also be introduced tentatively into models to evaluate the effects of adjustment for possible effects associated with some managers undertaking these assessments earlier than others and earlier than control group participants.

Similar analyses of scaled secondary manager outcomes will assess differential change due to intervention arm. Mathematical transformation or categorisation of raw scores may be undertaken to meet distributional assumptions and address any violation of assumptions attributable to outliers. Comparable analyses of employee measures will additionally accommodate the nesting of employees within managers by including a random effect for managers where this is possible.

Additional per-protocol analyses to assess effectiveness of the program will focus on managers who completed at least one of the three topics. This subgroup will be compared to all responders in the waitlist control group and, secondarily, with managers who completed less of the training material. The latter comparison will inform the dose-response profile of the intervention and, in particular, whether completing only a subset of the earlier components of *HeadCoach* has a benefit comparable to the complete program.

All tests of treatment effects will be conducted using a two-sided alpha level of 0.05 and 95% confidence intervals. A member of the research team who is blinded to the intervention and waitlist control allocations will perform this analysis. The nature of the intervention will make blinding managers to their group allocation impossible.

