### Sample size and power calculations

Our industry partners comprise a total of 42 geographical clusters with an average of 20 managers in each cluster. Participation in this study will be voluntary. Based on pilot data, we assume a conservative participation rate of 20% of all managers, with a drop-out rate of 25%. Based on these assumptions, we anticipate being able to recruit a minimum of 168 managers and to successfully follow up 126. Assuming an intraclass correlation of 0.05 yields a design effect of 1.15, the forecast achievable sample size would have 80% power to detect a moderate effect size of 0.54 using an alpha value of 0.05.

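### Adjusting the primary analysis for baseline confidence, rather than contrasting change from baseline with baseline left free, would gain precision at no cost

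*Protocol article*

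**What the plan says.** The Abstract of the protocol article defines the primary outcome as change from baseline in managers' confidence. The Statistical analysis section then says "A priori planned comparisons of change from baseline to the 4-month endpoint will test the primary hypothesis". The model is likelihood-based, with an unstructured covariance across measurement occasions and a random work-site factor.

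The same section names three kinds of adjustment term: stratification variables, variables found to be imbalanced, and time to the post-intervention assessment. All enter tentatively, and the first two stay only if significant and influential. The baseline confidence score is not named. The text does not say whether baseline is a response with free arm means, a response with arm means held equal, or a covariate.

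The Sample size and power calculations section starts from "a total of 42 geographical clusters with an average of 20 managers in each cluster" and continues "we anticipate being able to recruit a minimum of 168 managers and to successfully follow up 126". It adds "Assuming an intraclass correlation of 0.05 yields a design effect of 1.15" and concludes that "the forecast achievable sample size would have 80% power to detect a moderate effect size of 0.54 using an alpha value of 0.05". It gives neither a baseline to follow-up correlation nor the SD to which 0.54 refers.

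Two further facts bear on the fix. Under Managers, the baseline questionnaire comes before managers enter the training or are told to wait. Under Study design, zones are randomised before recruitment.

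**The concern.** If baseline is one of the repeated responses and each arm has its own baseline mean, the planned contrast is the arm difference in mean change. It subtracts the whole observed baseline difference, although only a fraction r of that difference is expected to persist to 4 months. The excess adds noise to the estimate. It also over-corrects for any chance baseline difference whenever r is below 1.

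Using the baseline score as a covariate subtracts only the part that predicts the outcome. Under the usual model this is never less precise, and the data are already collected. At stake is precision in a trial whose size is set by how many managers the partners can supply. The validity of the test is not at stake.

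**Working it through.** **Inputs from the document.** 42 clusters averaging 20 managers, 20% participation, 25% drop-out, ICC 0.05, design effect 1.15, effect size 0.54, two-sided alpha 0.05.

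**Assumptions.** Equal allocation, equal SD at both occasions, and r from 0.3 to 0.7. The 6-week score is left out of the calculation.

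**1. The plan's own figure.**
- Recruited: 42 × 20 × 0.20 = 168. Followed up: 168 × 0.75 = 126.
- Design effect: 1 + (4 − 1) × 0.05 = 1.15.
- Effective sample: 126/1.15 = 109.6, or 54.78 per arm.
- Power at 0.54 with unit SD: 80.7% (normal approximation) or 80.0% (noncentral t).
- Detectable effect with unit SD: (1.960 + 0.842) × √(2/54.78) = 0.535.

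The stated 80% is reproduced without any correlation term.

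**2. Variance of the two estimators**, relative to an unadjusted comparison of 4-month scores among the 126.
- Free baseline, likelihood-based: managers lost to follow-up still contribute their baseline. The relative variance is V = (1 − r²) + (126/168)(1 − r)² = (1 − r²) + 0.75(1 − r)².
- Baseline-adjusted: V = 1 − r².

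The power columns use Φ(0.54/√(2V/54.78) − 1.96) and apply **only if 0.54 is in raw-score SD units**.

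| r | V, free baseline | V, adjusted | Variance saved | Power, free | Power, adjusted |
|---|---|---|---|---|---|
| 0.3 | 1.278 | 0.910 | 29% | 71% | 84% |
| 0.5 | 0.938 | 0.750 | 20% | 83% | 90% |
| 0.7 | 0.578 | 0.510 | 12% | 96% | 98% |

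**3. Detectable effect at r = 0.5, in raw-score SD.**
- Free baseline: 0.535 × √0.938 = 0.52.
- Adjusted: 0.535 × √0.750 = 0.46.

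**4. Cluster intercept modelled.** A cluster intercept that is constant over time largely cancels from a change contrast, so a flat design effect is harsh on it. A generalised least squares calculation used 42 clusters of 4 managers (3 followed up), a random intercept with ICC 0.05 and an unstructured residual. Its adjusted version holds baseline arm means equal, so the savings are approximate for covariate adjustment.

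| r | Variance, free | Variance, adjusted | Saved |
|---|---|---|---|
| 0.3 | 0.0404 | 0.0302 | 25% |
| 0.5 | 0.0297 | 0.0245 | 17.5% |
| 0.7 | 0.0183 | 0.0164 | 10% |

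**5. Where power would reach 80%, if 0.54 is in raw-score SD.** Solve 0.5353 × √V = 0.54, so V = 1.018. With the free-baseline formula, 1.75 − 1.5r − 0.25r² = 1.018 gives r ≈ 0.45. With the cluster intercept modelled, the threshold is r ≈ 0.36. If 0.54 is in SD-of-change units, power for a simple change-score comparison is 80.7% at every r.

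**6. Over-correction.** The SE of the baseline arm difference is about 2 × √(1.15/168) = 0.17 SD, so a chance difference of 0.32 SD or more arises about 1 time in 20. The change contrast over-corrects by (1 − r) times the difference. At r = 0.5 that is 0.16 SD, about 30% of 0.54.

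**The case against.** The strongest objection is that the document does not say baseline is left free. A contrast described as change from baseline could come from a model with baseline as a covariate or with baseline means held equal, and then nothing is lost. A condensed article may leave that detail to an analysis plan. This stands in part: the free-baseline reading is an inference. But the article itself fixes the contrast, the covariance structure and the rule for covariates. Its list of adjustment terms omits the baseline score. If that score entered under the imbalance rule, it would be kept only if significant and influential.

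Second, the planned contrast is valid, matches the outcome as the Abstract defines it, and is unbiased over randomisation. That stands. The over-correction is conditional on an observed imbalance.

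Third, a reader might infer a larger loss and a failed power calculation: 35%, 25% and 15% of variance at r = 0.3, 0.5 and 0.7, from (1 − r)/2, with power missed whenever r is below about 0.5. The documents do not support this. Those figures describe a change score in completers only, whereas the planned likelihood model keeps the baselines of managers lost to follow-up. The power shortfall also requires 0.54 to be in raw-score SD units, which is nowhere stated. Given how the Abstract defines the outcome, scaling to the SD of change is at least as natural, and then there is no shortfall.

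**Conclusion.** This is a free improvement, not an error in the test. On the likeliest reading, the primary contrast gives up between about 10% and 29% of the variance for r from 0.7 down to 0.3. The exact figure depends on r and on how clustering is handled. The range rests on an assumed correlation, equal allocation and the inferred free baseline. If the sponsor already intends to adjust, there is no loss and one sentence settles the matter.

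The power statement is not shown to be wrong. Only on the raw-score SD reading would the planned contrast fall below 80%, at r under about 0.45 (design effect 1.15) or 0.36 (cluster intercept modelled). Above those values it would exceed 80%.

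**What to change.** State the primary estimate as the arm difference in the 4-month confidence score, from the mixed model of the 6-week and 4-month scores. Include baseline score by visit as a covariate, kept whatever its significance or balance.

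Covariate adjustment is preferable here to holding arm means equal at baseline. Zones are randomised before managers are recruited, so randomisation does not guarantee equal baseline means among those who opt in. Managers with only a baseline score drop out of the covariate model's likelihood. That costs no precision in the comparison above, since the adjusted variance already rests on the 126 followed up.

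Apply the same approach to the scaled secondary manager and employee outcomes; for employees this means the 4-month score adjusted for baseline. Keep the raw change contrast as a sensitivity analysis. In the sample size section, state which SD scales 0.54 and, if it is the raw-score SD, the correlation assumed.

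The cost is wording in the analysis plan. No new data are needed, because every participating manager is asked for the baseline score before being directed to the training or told to wait.
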